### Clinical management of patients in the trial

Patients involved in this trial will be managed according to best practice established on the ICU. In patients where there is a clinical indication for acute and immediate treatment with a statin after randomisation, such as an acute myocardial infarction, the study drug will be discontinued and a statin commenced. The patient will not be unblinded and data collection will continue. This will be recorded on the CRF. The number and dose of any antipsychotics or additional psychotropic drugs given to a study patient in the first 28 days or before discharge from the ICU (whichever is the earlier) will be recorded in the CRF. The daily sedation goal for all patients will be a RASS score of 0 to −1, unless a patient’s clinical condition requires a deeper level of sedation, such as a patient with severe acute respiratory distress syndrome, or the patient is weaned from ventilation. The sedative drugs used before patients are consented for the study will be decided by the responsible intensivist. Once they have consented to participate in the study, patients will be maintained using fentanyl (manufacturer: Hameln Pharmaceuticals, Gloucester, UK) and propofol (manufacturer: UAB Norameda, Klaipeda, Lithuania) infusions as needed while requiring ventilation. The infusion rate will be titrated according to RASS assessment and the nurse’s judgment of when a patient is experiencing pain. Daily sedation breaks and daily spontaneous breathing trials will be done at the discretion of the consultant intensivist responsible for clinical management, according to routine unit practice. The sedative infusions will not be restarted as long as the patient tolerates the interruption of sedation drugs.

### Study procedures for unblinding

As a placebo-controlled, double-blind trial, patients and clinicians will be blinded to each patient’s allocation. All trial drugs, whether simvastatin or placebo, will be packaged identically and identified only by a unique trial identifier. Any consultant intensivist may request emergency unblinding on safety grounds. This option should be used only if the patient’s future treatment requires knowledge of the treatment assignment. If a consultant decides that there is justification to unblind a patient, they should attempt to contact the CI or site co-investigator, who will arrange for them to discuss the necessity of unblinding with a clinical member of the trial team. Emergency unblinding will be performed by the on-call pharmacist. The NICTU should also be informed that unblinding has occurred. All events will be logged.

### Data collection and management

All study data for an individual patient will be recorded in the CRF. Patients are identified by initials and their unique trial identifier, which was allocated at the time of randomisation. Data will be collected from the time the patients are enrolled into the trial through to and following their discharge from hospital, up to a maximum of six months following recruitment. Any history of alcohol abuse will be recorded if documented in the medical records. PREdiction of DELIRium in ICu patients (PRE-DELIRIC) and daily Sequential Organ Failure Assessment (SOFA) scores will be calculated using data from patients’ clinical notes. The PRE-DELIRIC is a validated delirium prediction tool for adult intensive care patients [25]. The SOFA score will be used as daily severity of illness assessment of ICU patients.

All completed CRFs will be forwarded to the NICTU, and submitted data will be reviewed and processed as per the NICTU Standard Operating Procedures. Due care will be taken to ensure data safety and integrity, and compliance with the Data Protection Act 1998. The trial identifier, name, address and other contact details of all patients who survive will be kept separately to allow patients to be contacted at six months for the telephone cognitive status evaluation, and for the follow-up questionnaires to be posted to them. No patient-identifiable data will be submitted to the NICTU. All essential documentation and trial records will be stored in conformance with the applicable regulatory requirements, and access to stored information will be restricted to authorised personnel. Trial documentation and data will be archived for at least five years after completion of the trial and as per sponsor requirements.

### Pharmacovigilance

EU Clinical Trials Directive 2001/20 provides the definitions of adverse events and reactions used in this trial (Table 1).

**Table 1 Tab1:** **Definition of adverse events and reactions according to EU clinical trial directive 2001/20**

**Term**	**Definition**
Adverse Event (AE)	Any untoward medical occurrence in a patient or clinical trial subject to whom a medicinal product has been administered, including occurrences which are not necessarily caused by or related to that product.
Adverse Reaction (AR)	Any untoward and unintended response to an investigational medicinal product related to any dose administered.
Unexpected Adverse Reaction (UAR)	An adverse reaction, the nature or severity of which is not consistent with the information about the medicinal product in question set out in the summary of product characteristics (or Investigator brochure) for that product.
Serious Adverse Event (SAE), Serious Adverse Reaction (SAR) or Suspected Unexpected Serious Adverse Reaction (SUSAR)	Respectively, any adverse event, adverse reaction or unexpected adverse reaction that:
	● results in death
	● is life-threatening
	● requires hospitalization or prolongation of existing hospitalization
	● results in persistent or significant disability or incapacity
	● consists of a congenital anomaly or birth defect^1^
	● is any other important medical event(s) that carries a real, not hypothetical, risk of one of the outcomes above

^1^For this trial it is anticipated that all women of child bearing age admitted will have a pregnancy test. If, however, a subsequent pregnancy is discovered the pregnancy will be followed in order to assess the outcome regarding any adverse event.

Because this study is recruiting a population that is already in a life-threatening condition, it is expected that many of the participants will experience adverse events. Events that are expected in this population (that is, events that are in keeping with the patient’s underlying medical condition) will not be reported as adverse events. An adverse reaction is an adverse event which is related to the administration of the study drug. If any adverse reactions arise, they will be reported on the adverse event form within the CRF. If an SAE thought to be related with the study drug occurs, reporting will follow the regulatory requirements and will be reported to the NICTU and the sponsor within 24 hours of becoming aware of the event. All SUSARs will be the subject of expedited reporting.

### End of trial

The trial will end when 142 patients have been recruited. The Data Monitoring and Ethics Committee (DMEC) will meet every nine months to determine whether there is any reason why recruitment should not continue. Interim analyses will only be undertaken at the request of the DMEC and will only be available to the DMEC. The trial will be stopped prematurely if mandated by the Ethics Committee, mandated by the Medicines and Healthcare products Regulatory Agency, decided by the Trial Steering Committee (TSC) or Sponsor after consideration of recommendations from the DMEC or funding for the trial ceases. The main criteria for early stopping of the trial by the TSC upon suggestions from the DMEC will be that evidence provided by the trial investigators from the trial and from other sources suggests: proof beyond all reasonable doubt that for all, or for some types of patients, the treatment regimen is clearly indicated or contraindicated, and evidence that might reasonably be expected to influence routine clinical practice.

### Statistical analysis plan

Analyses of effectiveness endpoints will be on an intention-to-treat basis. The primary outcome (delirium/coma free days) is a heavily skewed distribution (bimodal with peaks at 0 and 14 days) and the groups will initially be analyzed by t-test with difference in means and 95% confidence intervals (CI) presented. A secondary analysis of these outcome measures involving a bootstrapped t-test will also be conducted to support the findings of the t-tests and confirmed using the Mann–Whitney non-parametric test. Dichotomous outcomes will be analysed using risk ratios and 95% confidence intervals, where appropriate. Continuous variables over time will be analysed by generalised linear modelling. Time to event outcomes such as duration of hospital stay will be analysed by survival methods and reported as hazard ratios and 95% CIs. Primary analyses will be based on patients with outcome data (that is, available case analysis). The randomisation process will ensure balance in baseline variables. A detailed analysis plan will be developed during the trial and submitted to the DMEC for review prior to the commencement of analysis. All analyses will be conducted at the 5% level of significance unless adjustment for multiple testing is needed.

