### Power and sample size estimate

The sample size calculation for this study has been initially based on data from the Awakening and Breathing Controlled trial published in 2008, using the mean delirium- and coma-free days of 10 at 28 days among patients without the study intervention [24]. Our pilot data showed a standard deviation of 4.14 in delirium and coma free days at day 14 in a similar cohort ([name], personal communication, September 2012) Assuming this standard deviation, and assuming a type I error of 0.05 and 80% power, a sample size of 64 patients per group is adequately powered to detect a difference of approximately 2 DCFDs between the intervention and control groups, or approximately 0.5 SD. Allowing for an estimated 10% loss to follow-up, the sample size required is 142. nQuery AdvisoR version 4.0 was used for the sample size analysis (Elashoff, JD 2000).

A flow chart for the protocol is outlined in Figure 1.

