Patient drug packs will be prepared by Victoria Pharmaceuticals (Belfast, UK), and distributed to the site. The 142 consecutive packs will contain either simvastatin or placebo according to a prearranged order dictated by the 1:1 variable block randomisation schedule decided by the use of a random number generator. Simvastatin (40 mg tablets) or identical placebo tablets will be packaged in a white opaque high-density polyethylene plastic container, which will be sealed with a tamper-evident seal and labelled in compliance with applicable regulatory requirements. The placebo and active tablets will be indistinguishable when crushed and dispersed in water for nasogastric tube administration. Each container will contain 70 tablets of the study drug for the treatment of one patient for 28 days (plus seven days coverage). Each pack will be numbered with the patient’s trial identifier. Treatment allocation will be blinded as all trial drugs will be packaged identically and identified only by a unique trial identifier. Recruited patients will be randomised to receive once daily simvastatin (80 mg, as two 40 mg tablets) or two identical placebo tablets administered enterally via a feeding tube or orally for up to 28 days.

Although the primary outcome is determined at 14 days, the study drug will be administered for up to 28 days in order explore if longer treatment is associated with sustained and greater effect; however, the 28 day measurement will be less reliable given an expected median ICU length of stay of nine days. The recruiting clinician will complete a trial prescription form detailing the unique trial identifier assigned to the patient at the time of randomisation, which also corresponds to the study drug pack to be prescribed. The first dose of the study drug will be administered as soon as possible, ideally within four hours of randomisation and after baseline samples are collected, and subsequent doses will be given at 12:00 am on the following calendar day. If, for any reason, a dose is not administered at the intended time, it may be administered subsequently, but not more than 12 hours after the intended time of administration. Any missed doses will be recorded in the CRF to monitor treatment compliance.

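### Randomisation is said to guarantee baseline balance, which unstratified blocks cannot do, and every stated primary-outcome analysis leaves out prognostic scores the trial already collects

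*Protocol article*

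**What the plan says.** The Statistical analysis plan section of the protocol article states without qualification: "The randomisation process will ensure balance in baseline variables". For the primary outcome, 14-day delirium- and coma-free days, it says that "the groups will initially be analyzed by t-test with difference in means and 95% confidence intervals (CI) presented". A bootstrapped t-test and a Mann–Whitney test support this. None of the three is described as adjusted for a covariate.

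The Trial conduct section describes allocation as a "1:1 variable block randomisation schedule" and names no stratification or minimisation factor.

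Several prognostic measures are collected. The Data collection and management section has PRE-DELIRIC and daily SOFA calculated from the notes, and adds: "The PRE-DELIRIC is a validated delirium prediction tool for adult intensive care patients". Under Clinical outcome measures, IQCODE is scored at recruitment as a measure of prior cognitive function. Covariate adjustment is mentioned once, for costs and QALYs in the Health economic analysis section. A detailed analysis plan is to be written during the trial; it is not among the documents shown.

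**The concern.** Blocking keeps the two arms close in size. It does nothing to make them alike in delirium risk, illness severity or prior cognition. In a trial of 142, sizeable chance differences in such factors are ordinary, so the sentence claims a property the design does not have.

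Two things are at stake. If a strongly prognostic factor happens to differ between the arms, the unadjusted difference in that particular trial is displaced, and neither supporting test can show or correct this because both are unadjusted too. Also, the baseline scores could narrow the confidence interval at almost no cost, in a trial sized at only 80% power. An adjustment chosen after an imbalance has been seen would be open to the charge of data-driven covariate selection, so the choice has to be made in advance.

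**Working it through.** **Inputs.** From Power and sample size estimate: SD 4.14 days ("Our pilot data showed a standard deviation of 4.14 in delirium and coma free days at day 14"); target "a difference of approximately 2 DCFDs between the intervention and control groups, or approximately 0.5 SD"; "assuming a type I error of 0.05 and 80% power"; 64 evaluable per group; 142 in total after 10% loss. Sidedness is not stated. Two-sided is assumed, because 95% intervals are planned and it reproduces the stated figure. The correlation ρ between the baseline scores (jointly) and the outcome is **not in the documents**; the range 0.2 to 0.5 is an assumption.

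**1. The plan's own figure.** 0.5 SD = 0.5 × 4.14 = 2.07 days. Normal approximation: n = 2(1.960 + 0.842)² / 0.5² ≈ 62.8, so 63 per group. With the noncentral t the answer is 63.8, so 64, with power 80.1%. Then 64 × 1.1 = 70.4, so 71 per arm and 142 in total. The sample size is reproduced. (For a difference of exactly 2.00 days, power at 64 per group is 77.4%.)

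**2. Chance imbalance.** For a standardised covariate, the difference in arm means has standard error √(2/n).

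| n per arm | SE | P(>0.20 SD) | P(>0.25 SD) | P(>0.30 SD) |
|---|---|---|---|---|
| 71 | 0.168 | 23% | 14% | 7% |
| 64 | 0.177 | 26% | 16% | 9% |

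For at least one of three independent covariates beyond 0.25 SD with 71 per arm: 1 − (1 − 0.136)³ ≈ 0.36. Positive correlation among the three would lower this.

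**3. Displacement given an imbalance.** Shift = ρ × SD × imbalance. For an imbalance of 0.25 SD:
- ρ = 0.2: 0.2 × 4.14 × 0.25 = 0.21 days, 10% of 2.07.
- ρ = 0.3: 0.31 days, 15%.
- ρ = 0.5: 0.52 days, 25%.

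This is a conditional shift in trials with that imbalance. It is not bias over repeated randomisation.

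**4. Precision from adjustment.** Residual SD = 4.14 × √(1 − ρ²); 64 per arm; difference 2.07 days; CI half-width = 1.979 × residual SD × √(2/64).

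| ρ (assumed) | Residual SD | Power | CI half-width (days) |
|---|---|---|---|
| 0 (unadjusted) | 4.14 | 80.1% | 1.45 |
| 0.2 | 4.06 | 81.7% | 1.42 |
| 0.3 | 3.95 | 83.7% | 1.38 |
| 0.4 | 3.79 | 86.5% | 1.33 |
| 0.5 | 3.59 | 90.0% | 1.25 |

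**5. Error rates by simulation.** 20,000 null trials per scenario, 64 per arm, with a 0–14 outcome peaking at both ends. Over all trials the t-test rejected in 5.3% (ρ = 0.3) and 5.0% (ρ = 0.5). Among the roughly 9% of trials with a covariate imbalance above 0.30 SD, it rejected in 8.7% and 14.2%, against 4.8% and 5.6% for the adjusted analysis. The simulated outcome had SD 5.3, not 4.14, so these rates are illustrative.

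**The case against.** The strongest reply is that nothing in the primary analysis is wrong. Under randomisation the unadjusted difference in means is unbiased, and its standard error already allows for chance imbalance. The sample size was computed for that comparison and is met, so adjustment would be a bonus the trial did not take. All of this stands. A reader might infer that the t-test is biased or invalid, or that 142 patients are too few on this ground; steps 1 and 5 of the working show neither.

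A reader might also infer that the t-test was chosen because balance was thought to be guaranteed. The article never makes that link. The two statements stand apart in the same section, so any causal connection is conjecture.

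The detailed analysis plan may add adjusted analyses, and the article says only that the t-test comes initially. The absence of supporting adjusted analyses from an article is therefore no fault in itself. But a later plan would not make the balance sentence true, and the method the article does name for the primary outcome is unadjusted.

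The benefit is also uncertain. PRE-DELIRIC is described as predicting delirium, whereas the outcome also counts coma and death. At ρ = 0.2 the gain is under 2 percentage points of power. This limits how strongly the change can be pressed, but does not remove the reason for it.

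**Conclusion.** The point holds in a limited form. The balance statement is incorrect as written: with 71 per arm and no stratification described, a given covariate has a 14% chance of differing by more than 0.25 SD, rising to about 36% for at least one of three if they are independent. The unadjusted t-test remains valid overall, at about 5% error across all randomisations. What is lost is precision, together with protection in those trials where a prognostic factor happens to be imbalanced. Adjustment would lift power at 0.5 SD from 80% to about 82–90% with 64 per arm, and this range rests entirely on the assumed ρ of 0.2 to 0.5. It is a worthwhile improvement and a factual correction; it does not threaten the trial's validity.

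**What to change.** Replace the claim of guaranteed balance with balance in expectation.

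Specify, before unblinding, a linear regression of 14-day delirium- and coma-free days on treatment, reporting the adjusted mean difference and 95% CI with robust or bootstrap standard errors. Adjust for:
- PRE-DELIRIC and SOFA, restricted to data recorded before the first dose. The article does not give the timing of PRE-DELIRIC and describes SOFA as daily. The first dose is ideally given within four hours of randomisation, so a day-1 SOFA could include values from after dosing.
- Recruitment IQCODE, with a simple imputation rule stated in advance. It is completed by a personal representative, relative or friend, and a patient entered through a professional representative may have no informant.

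Keep the unadjusted t-test, bootstrapped t-test and Mann–Whitney test alongside it.

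The cost is a change to the stated primary model before analysis, some missing baseline values to handle, and little return if the correlations prove weak. No new data collection is needed beyond confirming when the scores were recorded. The article reports 99 of 142 patients recruited with the detailed plan still to go to the monitoring committee, so that plan is the natural place for the change.

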### Health economic analysis

A within-trial cost-utility analysis (CUA) will be undertaken by the health economist to assess the cost-effectiveness of simvastatin compared with placebo in the prevention and treatment of delirium. The perspective of the analysis will be the NHS and Personal Social Services. The outcome of the CUA will be the cost per QALY gained. Patients’ EQ-5D-5 L responses will be presented as utility scores and used to calculate QALYs at six months. Resource use will be valued using national sources of unit costs, such as the NHS Reference Costs and Personal Social Services Research Unit Costs of Health and Social Care [26,27]. Multiple regression models will be used to estimate mean costs and QALYs for the six-month study period, adjusted for covariates. An incremental cost-effectiveness ratio will be calculated to estimate the cost per QALY gained. Patient-level cost and QALY data will be bootstrapped, and a cost-effectiveness acceptability curve will be derived to show the probability of simvastatin being cost-effective compared to a placebo, at various thresholds of willingness-to-pay for an additional QALY. Sensitivity analysis will be performed to explore the impact on cost-effectiveness of variations in key parameters. Given the study timeframe, discounting will not be necessary.

### Trial oversight

The CI will assume overall responsibility for ensuring the trial is run in accordance with GCP and to the highest ethical and scientific standards. West Hertfordshire Hospitals NHS Trust Research and Development Department will be responsible for overseeing the financial management of the trial, and as Sponsors, for ensuring that statutory regulations and reporting requirements are fulfilled. Day-to-day management of the trial will be undertaken by the local study team who will liaise on monthly basis with the Trials Management Group, composed of the CI and supporting staff both at the site and at the NICTU.

The TSC will be comprised of experienced critical care personnel and trialists, as well as a lay representative from ICUsteps, an ICU patient support charity. This charitable trust was founded in 2005 by ex-patients, their relatives and ICU staff to support patients and their families through the recovery from critical illness. The TSC will take responsibility for major decisions, such as a need to change the protocol for any reason, monitoring and supervising the progress of the trial, reviewing relevant information from other sources, considering recommendations from the DMEC, and informing and advising on all aspects of the trial. The DMEC (equivalent to a North American Data Safety Monitoring Board) will be appointed independently from the study team, comprising of at least two clinicians with experience in undertaking clinical trials and caring for critically ill patients and a statistician. The study statistician will provide a report to the DMEC. The DMEC will function primarily as a check for safety reviewing adverse events. They will specifically review the incidence and severity of side effects, SAEs and SUSARs, and produce a safety recommendation following each meeting.

On-site monitoring visits will be undertaken by the Clinical Trials Unit, and will be conducted in accordance with the study monitoring plan. On-site monitoring will be an ongoing activity from the time of initiation until study close-out, and will comply with the principles of GCP and EU directive 2001/20/EC.

Before the study starts, an initiation visit will take place to ensure that all relevant essential documents and trial supplies are in place, and that site staff are fully aware of the study protocol and Standard Operating Procedures. During the study, on-site monitoring visits will check the following: the completeness of patient records; the accuracy of entries on CRFs; the adherence to the protocol, Standard Operating Procedures and GCP and the progress of patient recruitment. Monitoring will also ensure that the study drug is being stored, dispensed and accounted for according to specifications.

